### Statistical Analyses

#### Statistical Analysis of Primary Outcome

The estimates of the volumes, from the T1-weighted 3D anatomical scans of the caudate nuclei (mm^3^), will be exported to a spreadsheet for regression analysis to assess the association between volume of caudate nuclei and secondary hyperalgesia areas. The association of the volume of the left and right caudate nuclei and the area of secondary hyperalgesia will be investigated by linear regression of the estimated best linear unbiased predictors (EBLUPS) on the individual volumes of the left and right caudate nuclei. The ability of the volume of caudate nuclei to predict individual variation in the area of secondary hyperalgesia will be investigated by linear regression on the EBLUPS as a function of the individual volumes of the caudate nuclei.

Significance of the caudate nuclei as a predictor will be assessed by analysis of variance (ANOVA) methods and the predictive ability will be quantified by summary of prediction error, including 95% prediction interval for the prediction of the size of the area of secondary hyperalgesia. Relevant examples will be presented illustrating how accurately the volume of the caudate nuclei predicts the area of secondary hyperalgesia in the individual participants or vice versa. The association will be expressed in R^2^and prediction intervals for the area of secondary hyperalgesia given fixed values of the caudate nucleus’ volume. All analyses of structural MRI data (both in the primary, secondary, and exploratory outcomes) will be adjusted for age.

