### Outcomes

#### Primary Outcome

We aim to investigate the association between the volume of the left and right caudate nuclei and the size of the area of secondary hyperalgesia induced by brief thermal sensitization. The association will be expressed in adjusted and non-adjusted R^2^and prediction intervals for the area of secondary hyperalgesia, given fixed values of the caudate nucleus’ volume.

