### Sample Size Estimation

Based on results from a previous study [11], sample size calculations are based on a Z-test of the Fisher transformed Pearson correlation. With a true correlation of r=-0.4 between the area of secondary hyperalgesia and the caudate nuclei, and a significance level of 2.5% to 5% according to the single step method (refer to *Statistical Significance*), a sample size of 52 is needed to obtain a power of 0.80 (β=0.20).

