#### Statistical Analysis of Secondary Outcome #1

From the T1-weighted 3D anatomical scans, volume estimates of the cortical and subcortical brain areas relevant for pain processing (mm^2^, mm^3^) will be exported to a spreadsheet for regression analysis to assess the association between volume of the relevant areas for pain processing and areas of secondary hyperalgesia. The association of the volume of areas relevant for pain processing and the area of secondary hyperalgesia will be investigated by linear regression of the EBLUPS in relation to the volumes of individual areas relevant for pain processing. The association will be expressed in R^2^and prediction intervals for the area of secondary hyperalgesia given fixed values of the volume of the relevant brain areas for pain processing.

Significance of the predictor will be assessed by ANOVA methods and in cases of significance the predictive ability will be quantified by summary of prediction error, including 95% prediction interval. Relevant examples will be presented illustrating how accurately the volume of the individual areas relevant for pain processing predicts the area of secondary hyperalgesia in individual participants, or vice versa. The association will be expressed in R^2^and prediction intervals for the area of secondary hyperalgesia given fixed values of the caudate nucleus’ volume.

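### The primary analysis regresses shrunken EBLUPs on caudate volume, so the promised 95% prediction interval for the area will be too narrow unless it is corrected

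*Protocol article*

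**What the plan says.** The section on the primary outcome's statistical analysis makes EBLUPs the dependent variable of an ordinary regression: "linear regression of the estimated best linear unbiased predictors (EBLUPS) on the individual volumes of the left and right caudate nuclei". Predictive ability is handled the same way, by "linear regression on the EBLUPS as a function of the individual volumes of the caudate nuclei". The output is to include a "95% prediction interval for the prediction of the size of the area of secondary hyperalgesia", plus worked examples of how accurately volume predicts the area in individual participants.

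The Primary Outcome section gives this interval the same standing as R²: the association is expressed in R² and "prediction intervals for the area of secondary hyperalgesia, given fixed values of the caudate" nucleus volume. Secondary outcome #1 follows the same route (the association "will be investigated by linear regression of the EBLUPS in relation to the volumes of individual areas relevant for pain processing"), as do exploratory associations #1-4.

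The article does not describe the first-stage model, the number of area measurements per participant or the variance components. It mentions no reversal of the shrinkage and no adding back of within-person variance. On reliability it offers only the Introduction's remark that within-person variation in the area is small relative to variation between people.

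**The concern.** Naming EBLUPs presupposes repeat measurements, because one value per person cannot separate between-person from within-person variance. The EBLUP multiplies each participant's deviation from the overall mean by a factor λ below 1. If it then serves as the outcome of a second regression, two things follow. The slope is multiplied by λ, and the residual spread is that of the shrunken predictor, not of the area.

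An interval built from that residual spread is labelled as covering the area but does not cover it at 95%. The error always runs one way: caudate volume looks like a better individual predictor than it is. Individual prediction is what the interval and the worked examples are meant to show.

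**Working it through.** **The plan's own figure.** The article states that "sample size calculations are based on a Z-test of the Fisher transformed Pearson correlation", with r = -0.4, power 0.80 and a per-test level of 2.5% to 5%. Two-sided, n = ((z_α + z_power)/atanh(0.4))² + 3:
- α = 0.05: ((1.960 + 0.842)/0.4236)² + 3 = 46.7, so 47.
- α = 0.025: ((2.241 + 0.842)/0.4236)² + 3 = 55.96, so 56.

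The stated 52 lies between these and is not in question.

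**Inputs.** r = -0.4 comes from Sample Size Estimation ("With a true correlation of r=-0.4 between the area of secondary hyperalgesia and the caudate nuclei") and is taken here as the correlation with the participant's true area. ICC and the number of repeats k are not given. They are assumed: ICC 0.8 to 0.95 with k = 2 as the range that fits the Introduction's remark, and ICC 0.5 as an extreme.

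**Formulas**, with between-person SD set to 1 and within-person variance se² = (1 - ICC)/ICC:
- Shrinkage and slope multiplier: λ = k·ICC/(1 + (k - 1)·ICC).
- Residual variance of the EBLUP regression: λ - λ²r².
- Residual variance needed for the true area: 1 - r².
- Residual variance needed for one newly measured area: 1 - r² + se².
- Coverage: 2Φ(1.96·s_EBLUP/√(needed variance + (1 - λ)²r²)) - 1. The last term allows for the flattened line.

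**Direction.** The EBLUP interval is too narrow for the true area when λ - λ²r² < 1 - r², which reduces to r²(1 + λ) < 1. At r = -0.4 the left side is at most 0.16 × 2 = 0.32, so this holds for every λ below 1. The shortfall for a measured area is larger still.

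**Example, ICC 0.8, k = 2.** λ = 1.6/1.8 = 0.889. EBLUP residual variance = 0.889 - 0.790 × 0.16 = 0.762, SD 0.873. Needed SD is √0.84 = 0.917 for the true area and √(0.84 + 0.25) = 1.044 for one measured area. Width ratios are 0.953 and 0.836.

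| ICC (k = 2) | λ | width ratio, true area | width ratio, one measured area | coverage, true | coverage, measured |
|---|---|---|---|---|---|
| 0.5 | 0.667 | 0.842 | 0.569 | 89.8% | 73.3% |
| 0.8 | 0.889 | 0.953 | 0.836 | 93.8% | 89.9% |
| 0.9 | 0.947 | 0.978 | 0.919 | 94.5% | 92.8% |
| 0.95 | 0.974 | 0.990 | 0.960 | 94.8% | 94.0% |

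With k = 4 and ICC 0.8, λ is 0.941, the ratios are 0.976 and 0.856, and coverage is 94.4% and 90.7%.

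**Simulation** (n = 52, 4000 runs, variance components estimated). With k = 2 and ICC 0.8, the mean EBLUP slope was -0.355 against a true -0.4, with coverage 93.2% (true) and 89.4% (measured). With ICC 0.9 it was -0.378, with 94.2% and 92.8%. Regressing unshrunken means gave -0.400 and -0.399.

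**What does not change.** With equal repeats the EBLUP is a linear rescaling of the participant mean, so the p-value and R² are identical (differences at rounding error in the simulation). With 10% of participants having one measurement instead of two, at ICC 0.7, power was 0.7515 against 0.751.

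**The case against.** The strongest reply has four parts.

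1. *The area is reliable.* The Introduction says so, which argues against an ICC of 0.5. This stands. A reader might take coverage near 74% as the expected size, but it requires within-person variance equal to between-person variance, which the article's description does not support. It is only an outer bound.

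2. *The target may be the true area.* The text does not say that the interval is for a single fresh measurement. Against a participant's true area the shortfall is only 1-5% of width at ICC 0.8 to 0.95. This stands, and it is why both targets are shown. Nor is all the shortfall for a measured area due to shrinkage. At ICC 0.8 and k = 2, unshrunken means with nothing added have residual SD √(0.84 + 0.125) = 0.982 against 1.044, which gives about 93.5% coverage compared with about 90% for EBLUPs.

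3. *The interval's construction is inferred.* The article is condensed, and a correction in the appendix or full protocol cannot be excluded. That limits certainty about what will be done. It does not remove the mismatch in the text, which names a shrunken outcome and promises an interval for the unshrunken quantity.

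4. *The confirmatory result survives.* A reader might infer that the primary test, R² or sample size is invalid. The documents do not support that: with equal repeats all three are untouched, and with mild imbalance practically so. The slope is biased, but it is not a named output.

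**Conclusion.** The point holds for the prediction interval and the individual examples drawn from it. If the text is followed as written, the 95% prediction interval for the area is too narrow at r = -0.4 for any reliability below 1, and the fitted line is too flat by the factor λ. At an assumed ICC of 0.8 to 0.95 with two repeats, the slope loses about 3-11%. The interval is about 1-5% too narrow for the true area (coverage about 93-95%) and about 4-16% too narrow for one measured area (coverage about 90-94%).

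The direction rests on the EBLUPs coming from a first-stage model without caudate volume, as the text reads, and on the interval using the second-stage residual spread. The size rests on an assumed ICC and k. Severity is moderate: a named part of the primary outcome would be misstated, while the hypothesis test and its power are not affected.

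**What to change.** Replace the two-stage analysis with one linear mixed model on the repeated area measurements, with caudate volume and age as fixed effects and a participant random intercept. Do not add intracranial volume as a further covariate. The section on T1-weighted images already adjusts all volumes for it, and adding it would adjust for head size twice.

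State which quantity the prediction interval is for:
- a participant's true area: use the between-person residual variance;
- a newly measured area: use the between-person residual variance plus the within-person variance.

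If two stages are kept, regress unshrunken participant means. Their residual variance already contains se²/k. For a new single measurement, therefore, add se²(1 - 1/k), not the whole of se²; for the true area, subtract se²/k. Check at ICC 0.8, k = 2: 0.965 + 0.125 = 1.09 and 0.965 - 0.125 = 0.84, the variances needed above.

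Apply the same to secondary outcome #1 and exploratory associations #1-4 wherever repeat measurements exist.

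The cost is analysis wording and a few lines of R. No new data are needed and the sample size stays as it is. The downside is wider reported intervals.

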#### Statistical Analysis of Secondary Outcome #1

From the T1-weighted 3D anatomical scans, volume estimates of the cortical and subcortical brain areas relevant for pain processing (mm^2^, mm^3^) will be exported to a spreadsheet for regression analysis to assess the association between volume of the relevant areas for pain processing and areas of secondary hyperalgesia. The association of the volume of areas relevant for pain processing and the area of secondary hyperalgesia will be investigated by linear regression of the EBLUPS in relation to the volumes of individual areas relevant for pain processing. The association will be expressed in R^2^and prediction intervals for the area of secondary hyperalgesia given fixed values of the volume of the relevant brain areas for pain processing.

Significance of the predictor will be assessed by ANOVA methods and in cases of significance the predictive ability will be quantified by summary of prediction error, including 95% prediction interval. Relevant examples will be presented illustrating how accurately the volume of the individual areas relevant for pain processing predicts the area of secondary hyperalgesia in individual participants, or vice versa. The association will be expressed in R^2^and prediction intervals for the area of secondary hyperalgesia given fixed values of the caudate nucleus’ volume.

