#### Statistical Analysis of Exploratory Associations #1-4

From the T1-weighted 3D anatomical scans, volume estimates of the caudate nuclei (mm^3^) will be exported to a spreadsheet for regression analysis to assess the association between volume of caudate nucleus and the score of HPDT, p-TS-max, p-TS VAS-AUC, PCS, and HADS respectively. The association of the volume of the right and left caudate nucleus and HPDT, p-TS-max, p-TS VAS-AUC, PCS and HADS will be investigated by linear regression of the EBLUPS in relation to the volume of caudate nucleus.

Significance of the ability of the caudate nucleus’ volume as a predictor will be assessed by ANOVA methods. The ability of the caudate nucleus’ volume to predict individual variations in HPDT, p-TS-max, p-TS VAS-AUC, PCS, and HADS will be investigated by linear regression on the EBLUPS of the individual volumes of the caudate nucleus. Significance of the caudate nucleus as a predictor will be assessed by ANOVA methods and in case of significance, the predictive ability will be quantified by summary of prediction error, including 95% prediction interval. Relevant examples will be presented illustrating how accurately the volume of the caudate nucleus predicts HPDT, p-TS-max, p-TS VAS-AUC, PCS, and HADS in individual participants, or vice versa.

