### Statistical Significance

Earlier studies have demonstrated that the volumes of the right and left hemispheric caudate nuclei are associated with one another [11]. To preserve a family-wise error rate of 5% for the two co-primary outcomes of associations between the right and left caudate nuclei and the area of secondary hyperalgesia, we will adjust for multiple comparisons of the co-primary outcomes. The two *P*-values will be evaluated at a significance level between 2.5% and 5% according to the single step method. For this method the significance level is determined by the correlation between the two resulting test statistics. If they are perfectly correlated the result will be 0.05, whereas if they are independent it will be 0.025.

*P*-values in the secondary and exploratory outcomes are evaluated at a 5% significance level, and to adjust for multiple comparisons, *P*-values are adjusted by means of single-step correction [49]. In the analysis of rs-fMRI data, the software’s standard methods and False-Discovery-Rate will be applied for correction for multiple comparisons.

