### Ethics

MRI uses a strong magnetic field and, unlike other imaging modalities, does not use radiation. MRI is non-invasive and has no known side effects. Due to the strong magnetic field, persons in the MRI room are not allowed to wear any metallic objects, and study participants will be informed of this prior to the MRI scans. Special MRI-compatible equipment will be used to monitor the participants inside the MRI scanner. Study participants will wear ear plugs and/or ear protection to avoid noise disturbances from the MRI scans, and will be equipped with an alarm call button in case of emergency.

A consultant radiologist will review all MRI scans. In the rare case of pathological findings, the radiology department at Bispebjerg and Frederiksberg Hospital has instructions for further treatment procedures. Briefly, the participant will be informed of the possible pathological findings and the participant will be scheduled for further radiological testing and referred to a specialist in neurology. Prior to inclusion in the study, participants will be informed of this procedure. If the participants do not wish to be informed of potential pathological findings, we reserve the right to exclude them before commencement of the MRI scan.

Likewise, the experimental pain testing conducted in the parallel study (Clinicaltrials.gov identifier: NCT02527395) do not cause damage to the skin or have any other long-term adverse effects. In rare cases, changes comparable with a first degree sunburn may appear. This study will be conducted in accordance with the principles of the Declaration of Helsinki. The protocol is approved by the local Danish Research Ethics Committees (identifier: H-15010473), and the Danish Data Protection Agency (identifier: RH-2015-149). This study is also reported on the international database (clinicaltrials.gov identifier: NCT02567318).

Informed written consent will be received from all volunteers before inclusion in the trial. Relevant provisions of the Research Ethics Committee regarding informed consent will be followed. Negative, positive, conclusive, and inconclusive test results will be published. We aim to publish the results in two separate publications, the first of which will report the primary and secondary outcomes, and the exploratory outcomes 1-4, and the second publication will report the exploratory outcomes 5 and 6.

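### Secondary outcome #1 and exploratory associations #1-4 summarise prediction only after a significant test; the secondary #1 section also contradicts itself on this and names the wrong predictor

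*Protocol article*

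**What the plan says.** All references are to the protocol article.

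- **Statistical Analysis of Primary Outcome.** After the ANOVA test, "the predictive ability will be quantified by summary of prediction error, including 95% prediction interval for the prediction of the size" of the hyperalgesia area. No significance condition is attached.
- **Statistical Analysis of Secondary Outcome #1, end of first paragraph.** The association is to be expressed in R² and "prediction intervals for the area of secondary hyperalgesia given fixed values of the volume of the relevant brain areas for pain processing". No condition is attached.
- **Same section, start of second paragraph.** After the ANOVA test, "in cases of significance the predictive ability will be quantified by summary of prediction error, including 95% prediction interval".
- **Same section, last sentence.** R² again, and "prediction intervals for the area of secondary hyperalgesia given fixed values of the caudate nucleus’ volume". No condition is attached, but the predictor is now the caudate.
- **Statistical Analysis of Exploratory Associations #1-4.** After the ANOVA test, "in case of significance, the predictive ability will be quantified by summary of prediction error, including 95% prediction interval". This section has no separate unconditional promise of R² or prediction intervals.
- **Secondary Outcomes.** The listed regions are primary somatosensory cortex, anterior and mid-cingulate cortex, putamen, accumbens, globus pallidus, insula and cerebellum. The caudate is not among them.
- **Statistical Significance.** P-values for the secondary and exploratory "outcomes are evaluated at a 5% significance level, and to adjust for multiple comparisons" a single-step correction is applied.

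**The concern.** Two things are wrong in the secondary #1 section as written. It gives incompatible rules for whether a non-significant region receives a prediction interval, and the choice between them could be made after the p-values are known. Its closing sentence, taken literally, would report the primary predictor's intervals under a secondary outcome.

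The condition is also a poor rule in itself, in both sections where it stands. A fit that passes a significance test at n=52 has, on average, a steeper slope and a smaller residual SD than the truth. If prediction is described only for such fits, readers see a selected and somewhat flattering set. The stated purpose is to show how well brain volume predicts an individual's response, and poor prediction is as informative for that purpose as good prediction.

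**Working it through.** **1. The rules side by side**

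| Section | R² | Prediction error summary and 95% prediction interval | Predictor named for the interval |
|---|---|---|---|
| Primary | unconditional | unconditional | caudate (correct) |
| Secondary #1, first paragraph | unconditional | interval unconditional | the region (correct) |
| Secondary #1, second paragraph, opening | not mentioned | only if significant | none named |
| Secondary #1, last sentence | unconditional | interval unconditional | caudate (not a secondary region) |
| Exploratory #1-4 | not mentioned | only if significant | caudate (correct here) |
| Secondary #2, exploratory #5-6 | not mentioned | none planned | not applicable |

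The contradiction is confined to secondary #1. In exploratory #1-4 the condition is the only rule for the prediction summary. The one tension there is that illustrative individual predictions are promised without condition.

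**2. The sample size used below**

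The Sample Size Estimation section gives r=-0.4, power 0.80, a significance level between 2.5% and 5%, a Fisher z test and n=52. With n = ((z₁₋α/₂ + z₀.₈₀)/atanh(0.4))² + 3 and atanh(0.4)=0.4236:

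- α=0.05: ((1.960+0.842)/0.4236)² + 3 = 46.7, so 47
- α=0.035: 51.5, so 52
- α=0.025: ((2.241+0.842)/0.4236)² + 3 = 56.0, so 56

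The figure of 52 is reproduced at a two-sided α of about 0.034, inside the stated range. It is not in dispute and serves only as the n for the next step.

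**3. What selection does at n=52**

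The set-up is simple linear regression on bivariate normal data, with 200,000 runs per true correlation. All runs are compared with those passing the threshold. The assumptions, which the protocol does not give, are:

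- true correlations of 0.2 and 0.3;
- a threshold of 0.05/8 as a conservative stand-in for the single-step correction over the eight listed regions, with hemispheres not counted separately;
- no age adjustment and no EBLUP step.

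| True r | Threshold | Share passing | Mean slope / true slope | Mean residual SD against truth |
|---|---|---|---|---|
| 0.2 | none | 100% | 1.0 | 0.5% low |
| 0.2 | 0.05 | 30% | 1.8 | 0.9532/0.9798, 2.7% low |
| 0.2 | 0.05/8 | 9% | 2.2 | 0.9280/0.9798, 5.3% low |
| 0.3 | none | 100% | 1.0 | 0.5% low |
| 0.3 | 0.05 | 59% | 1.3 | 0.9373/0.9539, 1.7% low |
| 0.3 | 0.05/8 | 28% | 1.5 | 0.9192/0.9539, 3.6% low |

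The true residual SD is √(1-r²) in units of the outcome SD: √0.96=0.9798 and √0.91=0.9539.

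**4. Effect on the interval itself**

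Take true r=0.2 and a participant one SD from the mean volume. The interval's centre is displaced on average by (1.8-1)×0.2 = 0.16 outcome SD at 0.05, and by (2.2-1)×0.2 = 0.24 at 0.05/8. The true half-width is about 1.96×0.98 = 1.92 SD. The displacement is therefore roughly 8% to 13% of the half-width. The selected slope is clearly biased, but the individual interval stays wide and is moved modestly.

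**5. Without the condition**

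The average slope equals the truth, the residual SD is within about 0.5%, and mean adjusted R² is 0.039 against a true 0.04 (r=0.2) and 0.087 against 0.09 (r=0.3).

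**The case against.** The strongest reply is that this is mostly drafting. Summarising individual prediction only where an association has been shown is a defensible reporting choice for secondary and exploratory outcomes. The caudate sentence is evidently carried over from the primary section, and the first paragraph of secondary #1 already names the right predictor. The width of the conditional intervals is barely affected.

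The point about width stands, and the intended predictor can be recovered. Neither settles which of the two rules in secondary #1 applies, and the slope that positions the interval is affected much more than the width.

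Three stronger readings are tempting, and the document does not support them.

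- **A fourfold inflation of R².** A reader might set the mean R² of 0.186 among results passing 0.05/8 against the true 0.04. But secondary #1 promises R² without condition, and exploratory #1-4 does not mention it. The contrast also blames selection for ordinary small-sample bias: with no selection the mean R² is already 0.058, and 0.186/0.058 is 3.2.
- **A breach of the publication promise.** The Ethics section says "Negative, positive, conclusive, and inconclusive test results will be published". Reporting the ANOVA result for every region and score would satisfy that, so it does not contradict a conditional prediction summary.
- **Loss of the distinction between a precise null and an imprecise estimate.** A prediction interval would not show this, because residual SD dominates its width. A confidence interval for the slope or correlation would.

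**Conclusion.** The point holds for secondary outcome #1 and exploratory associations #1-4 only. In secondary #1 the text is wrong as written: it contradicts itself on prediction intervals, and its last sentence names a predictor outside the secondary regions. In exploratory #1-4 there is no comparable contradiction; removing the condition there is a cheap improvement that matches the primary analysis.

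If the condition were followed, the reported slopes would be too steep when true associations are weak, by about 1.8 to 2.2 times at a true correlation of 0.2 and 1.3 to 1.5 times at 0.3. Interval width would be only slightly too narrow (about 3-5% and 2-4%). These sizes rest on assumed correlations, an illustrative threshold of 0.05/8 and a model without age or the EBLUP step. The bias shrinks as the true correlation grows. A reader should not extend it to all secondary and exploratory outcomes: secondary #2 and exploratory #5-6 plan no prediction summary, and the primary outcome carries no condition. The correction should be made, but the trial's main conclusion does not depend on it.

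**What to change.** 1. In Statistical Analysis of Secondary Outcome #1 and of Exploratory Associations #1-4, delete the phrase that makes the prediction summary depend on significance. State that R², prediction error and the 95% prediction interval will be reported for every pre-specified region and score, whatever the p-value.
2. In the last sentence of the secondary #1 section, replace the caudate nucleus' volume with the volume of the region analysed. Alternatively, drop the sentence, since the first paragraph already says this correctly.

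The same fitted models supply all the figures, so no new data or analysis is needed. The cost is a longer supplementary table.
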